### 6.2 Analysis Methods

*See section 3.7 “Statistical Analysis Outline”*

### 6.3 Missing Data

*See also the protocol section “Procedure For Accounting For Missing, Unused, And Spurious Data”*

For the analysis of each of the progression criteria, the following will apply:

1. Recruitment: missing data are not applicable, so they will not be imputed.
2. Engagement: missing data are not applicable, as instances of expected consultations with which participants do not engage will be coded as “no engagement” rather than as missing.
3. Adherence: It is plausible that weight data may be missing. Missing data will be imputed using methodology deemed appropriate by the Trial Statistician given the magnitude of the missing data and any other factors deemed relevant at the time. This imputation is likely to be through baseline observation carried forward, because of (a) the short duration (~4 weeks) between the two time points (screening and admission) during which weight typically remains relatively stable, (b) we

anticipate a relatively small proportion of missing data as the follow-up visit happens on admission to hospital, and (c) the total size of the study is small.

4. Retention: missing data are not applicable, so they will not be imputed.

#### 6.4 Sensitivity Analysis

No sensitivity analyses are planned. Should the data during the study begin to deviate from that expected (eg a non-nominal amount of missing data) then appropriate sensitivity analyses may be undertaken at the discretion of the Trial Statistician.

#### 6.5 Pre-specified Subgroup Analysis

*See also the protocol section "Description of the Statistical Methods"*

No subgroup analyses are planned.

#### 6.6 Supplementary/Additional Analyses and Outcomes

No supplementary analyses are planned.

#### 6.7 Harms

Safety is an outcome variable and its analysis is detailed elsewhere in this document in sections such as the section "Statistical Analysis Outline" and others.

#### 6.8 Health Economics and Cost Effectiveness (where applicable)

*See also the protocol section "Health Economic analysis"*

The health economics analysis plan will be reported separately.

### 7. VALIDATION OF THE PRIMARY ANALYSIS

*See also the protocol section "Description Of The Statistical Methods"*

To validate the primary outcomes a statistician not involved in the trial will independently repeat the analyses detailed in this SAP. The results will be compared and any unresolved discrepancies will be reported in the Statistical Report (See OCTRU SOP STATS-005 Statistical Report).

**Table 4: list of outcome variables subject to checks by uninvolved statistician**

| Type    | Subtype                  | Outcome variable (as defined in table 3)                                                                |
|---------|--------------------------|---------------------------------------------------------------------------------------------------------|
| Primary | 2. Engagement variable   | Proportion of phone calls answered                                                                      |
| Primary | 3. Adherence variable    | Proportion of intervention participants with $\geq 5\%$ weight loss from baseline to the day of surgery |
| Primary | 4. Retention variable    | Percentage at final follow-up                                                                           |
| Primary | 1a. Recruitment variable | Recruitment Rate                                                                                        |

|         |                          |                                        |
|---------|--------------------------|----------------------------------------|
| Primary | 1b. Recruitment variable | Number of sites open                   |
| Primary | 1c. Recruitment variable | Total number of participants recruited |

## 8. SPECIFICATION OF STATISTICAL PACKAGES

Any specific statistical analysis will be carried out using appropriate validated statistical software such as STATA, SAS, SPLUS, or R. Any other analysis done by the Trial Statistician will be done by that software deemed appropriate by the Trial Statistician. The relevant package and version number of any software used will be recorded in the Statistical Report.

## 9. PUBLICATION

*See also the protocol sections “Ethical And Regulatory Considerations”*

This study will be conducted as part of the portfolio of trials in the Surgical Intervention Trials Unit (SITU), a Royal College of Surgeons of England specialist trials centre dedicated to evaluating surgical intervention at the University of Oxford. It will follow their Standard Operating Procedures ensuring compliance with the principles of Good Clinical Practice and the Declaration of Helsinki and any applicable regulatory requirements.

## APPENDIX: GLOSSARY OF ABBREVIATIONS

**Table: Glossary of abbreviations**

| Abbr   | Meaning                                                                                     |
|--------|---------------------------------------------------------------------------------------------|
| CARE   | CARE feasibility randomised controlled trial                                                |
| DMEC   | Data Monitoring and Ethics Committee (DMEC)                                                 |
| RBP    | Randomisation and Blinding Plan                                                             |
| RCT    | Randomised Controlled Trial                                                                 |
| RRAMP  | Registration / Randomisation and Management of Product, a randomisation software for REDCap |
| SAP    | Statistical Action Plan                                                                     |
| SOP    | Standard Operating Procedure                                                                |
| TMF    | Trial Master File                                                                           |
| TSC    | The independent Trial Steering Committee (TSC)                                              |
| TSDMEC | Trial Steering, Data Monitoring, and Ethics Committee (TSDMC)                               |

## APPENDIX: STUDY FLOWCHART

[figure not shown]

[figure not shown]

## 1. INTRODUCTION

The CARE SAP includes this text

### *3.7.2 Secondary and other outcomes*

*Further details regarding the secondary outcomes will be provided at a later date, (provisionally in a supplementary document) prior to database lock.*

*Excerpt from CARE\_SAP\_v1.0\_14Mar2023.docx*

This is that supplementary document.

## 2. OVERVIEW

The secondary outcomes will be summarised descriptively by trial group. If appropriate, the effect size and 95% confidence intervals will be estimated with regression models. Both absolute and relative effect sizes will be reported.

Complications will be summarised using one or more of the following:

- count/percentage of participants with any complication
- count/percentage of participants with any complication by grade
- count/percentage of participants with the highest grade of complication reported
- count/percentage of participants with any type of complication
- count of total complications.

## 3. DEFINITION OF POPULATION FOR ANALYSIS

Main analysis: All randomised participants that underwent surgery will be included in the main analysis on an intention-to-treat basis (ITT) regardless of withdrawal or non-adherence. An intention-to-treat basis assigns all randomised participants to their originally allocated group, whether they received their allocated randomised treatment arm approach or not, or dropped out or not. Participants who had their surgery less than 20 days since randomisation will be included in this analysis.

Per-protocol analysis: We will also conduct an analysis on a per-protocol basis. A per-protocol basis includes only those randomised participants who met all eligibility criteria, had no major deviations from the study procedures, and adhered to their assigned interventions. For the intervention group, this includes the participants who achieved  $\geq 5\%$  weight loss from baseline to the day of surgery. For participants in the usual care group, this excludes those who lost  $\geq 5\%$  weight loss from baseline to the day of surgery. Participants who had their surgery less than 20 days since randomisation will not be included in this analysis.

Adverse events: The adverse event analysis will include the participants in the control group and the participants commencing the intervention in the intervention group.

## 4. USE OF MODELS

### 4.1 Input variables

The SAP states that the mean and 95% confidence intervals for the secondary outcome variables will be estimated with adjusted regression models. Those adjustments will be our four input variables, specifically:

- treatment group. There are two treatment groups, the control and the intervention.
- baseline value (where applicable)
- time point (where applicable)
- stratification variables. The two stratification variables are performance status (0 vs 1-2) and age at diagnosis ( $\leq$ / $\geq$ 70 years). These will be combined into one [1][2].

The extension from regression models to mixed models was not explicitly stated but is assumed. Such models will have fixed effects and may be further extended to include a random effect and/or an interaction. Details of those models include:

- The fixed effects are the adjustments
- The random effect is the participant/study ID
- The interaction is multiplicative. For example, an interaction between the treatment group and the time point (both of which are fixed) will be considered.

In models with interaction terms, the treatment effect will be the interaction term. In models without an interaction term, the treatment effect will be the treatment group.

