### 3.2 Randomisation and Blinding

*See also the protocol section “Randomisation” and “Blinding and code-breaking”*

Participants will be randomised by the local research team intended to conduct randomisation through a minimisation module on REDCap.

There are two arms, one for the intervention, one for the control.

Eligible participants will be individually randomised with a 1:1 allocation ratio to receive either the intervention or the control through minimisation with a 20% random element. The two stratified variables will be performance status (“0” vs “1-2”) and age at diagnosis (“< 70 years” and “≥70 years”) with the threshold of 70 chosen as the median age of diagnosis of colorectal cancer.

Allocation concealment is achieved as randomisation occurs after the baseline visit, the randomisation algorithm is unmodifiable and concealed from investigators and the local research teams, and the local research teams have no access to the total number of participants randomised to each group.

It is impossible to blind the participants and research nurses due to the nature of the intervention. Therefore, procedures for breaking the allocation code are not applicable. However, the assessors of the future primary outcome (research nurses conducting the post-operative follow-up visit) will be blinded. The central study team (chief investigator and members of the trial management committee) will be blinded to the adverse events and all post-operative data by trial group. The trial statistician is not blinded.

Full details of the randomisation are available in the latest RBP (Randomisation and Blinding Plan), which is stored in the confidential statistical section of the TMF.

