### 3.3 Sample Size, hypothesis testing, and progression decision

*See also the protocol section "Sample Size Determination"*

With 72 patients (n=36 per arm), the trial will be 90% powered at one-sided 5% level based on the normal approximation approach to detect whether the proportions for the engagement, adherence, and retention criteria in the table 1 are truly above the upper limit of the red zone (>50% engagement, >35% adherence, >65% follow-up) based on an alternative being in the green zone. The collective power for the three criteria of engagement, adherence, and retention is 85% ( $93\% \times 92\% \times 99\%$ ) at 5% level to detect "GO" signals, without multiple testing adjustment. Recalculating the sample size on a binomial approach (sensitivity analysis) provided almost identical estimates.

We are testing against the upper limit of the red zone when the lower limit of the green zone is hypothesised to be true, therefore:

- Null hypothesis: True feasibility outcome is not greater than the upper limit of the red zone.
- Alternative hypothesis: True feasibility outcome is greater than the upper limit of the red zone.

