## 15.4 Sensitivity Analyses

Sensitivity analyses will be done on at least the following:

- **Per-protocol analysis.** The per-protocol analysis will repeat the above models using the per protocol population as defined in section 3.
- **Stratification factors.** The two stratification factors are performance status (“0” vs “1-2”) and age at diagnosis (“< 70 years” and “ $\geq$ 70 years”). For sensitivity analysis we will do the following:
  - Repeat the models with an interaction term between age at diagnosis (“< 70 years” and “ $\geq$ 70 years”) and treatment. This will be expanded to “...and treatment and time” if time is an input variable, see below.
  - Repeat the models with an interaction term between performance status (“0” vs “1-2”) and treatment. This will be expanded to “...and treatment and time” if time is an input variable, see below.
  - Models measuring the state at one timepoint (eg discharge) or the state change between two timepoints will not need a time variable. Models measuring the state at two or more timepoints (eg baseline vs admission vs 30-days post-op) will need a time variable. In such cases, the interaction above will include the time variable. The paper at [7] is an example of this.
- **Other.** Other sensitivity analyses may be conducted if deemed necessary by the Trial Statistician.

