### 20.3 Linear mixed models: worked example

Consider this scenario:

*Arm ( $J=2$ ) indexed by the  $j$  subscript each see  $n_j$  patients. So our grouping variable is the arm. Each arm sees 36 patients. The total number of patients is the sum of the patients seen by each arm. In our example,  $N=72$ , so 72 patients were seen by two arms. Our outcome is a continuous variable, output weight. Furthermore we have 3 fixed effects predictors, baseline value, timepoint, and stratification variable, plus a fixed intercept and one random intercept ( $q=1$ ) for each of the  $J=2$  arms. For simplicity, we are only going to consider random intercepts. We will let every other effect be fixed for now. The reason we want any random effects is because we expect that output weights within arms may be correlated.*

So the formula is

$$y = xb + zu + e$$

That gives us this table below:

| Symbol | Description                                                                                                                                                                                           | Type              |
|--------|-------------------------------------------------------------------------------------------------------------------------------------------------------------------------------------------------------|-------------------|
| ny     | number of values of the outcome variable                                                                                                                                                              | 72                |
| np     | number of predictor variables                                                                                                                                                                         | 4                 |
| nj     | number of groups                                                                                                                                                                                      | 2                 |
| nq     | number of random intercepts per group                                                                                                                                                                 | 1                 |

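### The supplement's rule for which coefficient is the treatment effect is ambiguous for repeated-measures secondary outcomes, is not right throughout under any reading, and conflicts with its own worked example

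*Combined protocol and SAP*

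**What the plan says.** Supplement section 4.1 lists four inputs: treatment group, baseline value, time point and stratification. All enter as fixed effects. "The random effect is the participant/study ID", and a treatment-by-time interaction is to be considered. The reporting rule follows: "In models with interaction terms, the treatment effect will be the interaction term". For a model with no interaction, the treatment effect is the treatment-group coefficient.

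Section 15.4 says: "Models measuring the state at two or more timepoints (eg baseline vs admission vs 30-days post-op) will need a time variable". That example makes baseline a level of time. The same section repeats the models with age-by-treatment and performance-status-by-treatment interactions, extended to include time where time is in the model.

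Appendix 20.3 gives the only worked mixed model. Arm, with two levels, is the grouping variable and has a random intercept. The fixed effects are intercept, baseline value, time point and stratification. There are 72 outcome values. The reason given is: "The reason we want any random effects is because we expect that output weights within arms may be correlated".

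Main SAP section 3.7.2 lists treatment group, baseline value and stratification variables as regression terms, and defers detail to this supplement.

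**The concern.** An interaction coefficient has no fixed meaning. What it estimates depends on which rows are responses and which level is the reference, and section 4.1 gives neither. The same sentence can therefore name the correct estimate, a near-zero number or one of the opposite sign, according to how the analyst codes time. The rule also covers every interaction, including those added in section 15.4 to look at effect modification.

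The worked example does not settle the matter, because it departs from section 4.1 on the two points that count: which factor is random, and whether treatment is in the fixed part.

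At stake are the between-arm estimates for modelled outcomes with a baseline and two later visits: weight, fat-free mass (kg and %), EQ-5D-5L index and VAS, and HADS anxiety and depression. Sit-to-stand time has one later visit, so it is drawn in only if baseline is a response row. The protocol's lay summary names muscle mass and mental health among the reasons for running the trial, so these estimates would inform a definitive study.

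**Working it through.** **The plan's own figure.** The documents give no figure for this model. The power statement ("the trial will be 90% powered at one-sided 5% level based on the normal approximation approach") concerns single proportions; its product, 0.93 × 0.92 × 0.99 = 0.847, agrees with the stated 85%. No repeated-measures model enters it.

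**Inputs.** From the documents: 36 per arm, "individually randomised with a 1:1 allocation ratio"; weight at baseline, pre-operative assessment 4 and day 30. Assumed, because the documents give no between-arm difference in kg: effect d1 = -5 kg before surgery; d2 = -5, -2.5, 0 or -7 kg at day 30; participant SD 2 kg; residual SD 2 kg. Each scenario is 2,000 simulated trials with complete data, fixed effects by least squares.

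**Reading A: baseline is a covariate; the two later visits are responses.** With visit coded 0 before surgery and 1 at day 30:

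y = b0 + b1·arm + b2·visit + b3·arm·visit + b4·baseline + strata + participant + error

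The effect is b1 before surgery and b1 + b3 at day 30. So b3 = d2 − d1, the change in effect between visits. Without the interaction, the arm term is (d1 + d2)/2, a fair average effect.

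**Reading B: baseline is a level of time.** With baseline as reference, the two interactions are the effects on change from baseline, d1 and d2. Without interactions, the arm term averages three rows, and randomisation makes the expected baseline difference zero: (0 + d1 + d2)/3. That is two thirds of (d1 + d2)/2.

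| True d1, d2 (kg) | A: d2 − d1 | A: simulated interaction | B: simulated interactions | B, no interaction: (0+d1+d2)/3 | Average true effect: (d1+d2)/2 |
|---|---|---|---|---|---|
| -5, -5 | 0 | 0.01 | -5.01, -5.00 | -3.33 | -5.00 |
| -5, -2.5 | +2.5 | +2.48 | -5.01, -2.53 | -2.50 | -3.75 |
| -5, 0 | +5 | +4.98 | -5.00, -0.03 | -1.67 | -2.50 |
| -5, -7 | -2 | -1.99 | -5.00, -6.99 | -4.00 | -6.00 |

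Under Reading A the interaction was positive in about 50% of trials for the sustained effect and in 100% for both fading effects. Under Reading B, adding baseline as a covariate as well left the interactions unchanged.

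So Reading A makes the interaction sentence wrong and the other sentence acceptable. Reading B does the reverse.

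**Section 15.4 interactions.** An age-by-treatment coefficient is the effect in one age group minus the effect in the other. If the effect is -5 kg in both, it is -5 − (-5) = 0. The rule would call that zero the treatment effect under either reading. The same holds for performance status.

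**Section 4.1 against appendix 20.3.**

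| | Section 4.1 | Appendix 20.3 |
|---|---|---|
| Treatment | fixed effect | random intercept, 2 levels; no fixed term |
| Participant | random effect | absent |
| Rows | not stated | 72, with time point as a predictor |

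With time point in the model, 72 patients give 72 × 2 = 144 or 72 × 3 = 216 rows. Coded literally, the example returns an arm variance on 1 degree of freedom, with no treatment coefficient or confidence interval. In 200 fits per scenario, the predicted arm difference averaged -4.95 for a true -5 kg and -0.77 for a true -1 kg (-1.02 with arm fixed), so small effects are shrunk.

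**The proposed model.** Adjusted arm contrasts at each visit recovered the truth: -5.01 and -5.00; -5.01 and -2.53; -5.00 and -0.02; -5.00 and -6.99, with empirical SE about 0.7 kg.

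**The case against.** The best defence is that the rule is right under the reading that the supplement's own time points favour. Section 15.4 treats baseline as a level of time, and the outcome table lists baseline among the time points. The interaction is then the difference in change from baseline and is unbiased, whether or not baseline is also a covariate. This stands. It does not rescue the no-interaction sentence, does not say which of two interaction coefficients is reported, and does not cover the age and performance-status terms.

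Three stronger inferences are tempting, and the documents do not support them.

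- A reader might infer that a sustained benefit would be reported as no effect. That needs Reading A and an interaction that is actually fitted, and section 4.1 only says one will be considered. Results are also summarised by arm and, for these outcomes, largely by time point, so a difference of several kg would show in the tables.
- A reader might infer that the plan yields no treatment estimate. That needs appendix 20.3, a simplified theory illustration, coded literally against section 4.1 and main SAP section 3.7.2.
- A reader might infer intervals that are too narrow because within-person correlation is ignored. No specified model does that for a treatment coefficient: section 4.1 has a participant effect, and appendix 20.3 has no arm coefficient to put an interval around.

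The consequences are also bounded. These are secondary outcomes of a feasibility trial, without p-values, and the confidence intervals are declared descriptive.

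**Conclusion.** The point holds as an ambiguous rule that can give a wrong estimate, together with a contradiction in the worked example. No single reading makes both sentences of the section 4.1 rule right. Under one reading, the reported number is d2 − d1: near 0 for a sustained effect and opposite in sign for a fading one. Under the other, the no-interaction estimate is two thirds of the average effect. The mislabelling of the section 15.4 interactions holds under both, but only in sensitivity models.

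The algebra assumes complete, balanced visits and no expected arm difference at baseline. It does not depend on the kg values, which are assumptions that set only the size of the distortion. Progression criteria and sample size are unaffected. This should be fixed before database lock, the deadline that main SAP section 3.7.2 sets for the supplement; it does not threaten the trial's primary purpose.

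**What to change.** Replace the rule in section 4.1 with one specification for repeated-measures outcomes:

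- Responses: post-baseline values only.
- Fixed effects: arm, visit, arm-by-visit, baseline value and stratification factors.
- Random effect: participant intercept.
- Treatment effect: the adjusted arm contrast with 95% CI at each post-baseline visit.

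State that interactions with age or performance status describe effect modification and are not the treatment effect. Amend the section 15.4 example so that baseline is not a level of time in these models. Rewrite appendix 20.3 with participant as the grouping variable, arm as a fixed effect and one row per participant per post-baseline visit, or delete it.

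The cost is supplement wording and analysis code. No new data are needed.
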